#### Aim 4: analyze MISSION-Vet implementation using the factors specified by the implementation model RE-AIM (Reach, Effectiveness, Adoption, Implementation, and Maintenance)

RE-AIM [48] states that successful deployment of an intervention is mediated by the following factors: *Reach*—the proportion of individuals reached by the intervention; *Effectiveness*—the efficacy of the program under ideal circumstances; *Adoption*—the proportion of patients that used the intervention; *Implementation*—the extent the intervention was well-implemented; and *Maintenance*—whether the intervention was maintained. While GTO provides guidance for successful implementation, the RE-AIM model provides a heuristic to judge the success of that implementation.

*Data sources*. All aspects of the RE-AIM framework will be informed by data from case managers in the IU and GTO groups and the Veterans they serve.

*Measures and data collection*. Each RE-AIM measure below, using data collected from aims 1–3, will be calculated for both the IU and GTO groups:*Reach*—Obtained from aim 1, the Reach measure will be the percent of all eligible Veterans who receive MISSION-Vet with adequate fidelity (defined as the endorsement of at least 75 % of the items on the MISSION-Vet Fidelity measure).*Effectiveness*—Obtained from aim 3, effectiveness will be the percentage of all eligible Veterans *who receive MISSION*-*Vet with adequate fidelity* who improve on each outcome in an amount consistent with a statistically significant effect.*Adoption*—The proportion of case managers who have more than 50 % of their eligible Veterans engaged in MISSION-Vet will be judged to have “adopted” MISSION-Vet as a standard protocol for Veterans with mental illness and co-occurring substance abuse disorders.*Implementation*—The extent to which the MISSION-Vet intervention was well implemented will come from aim 1 and be expressed as the percentage of eligible Veterans who actually participated in MISSION-Vet who had adequate fidelity (endorsement of at least 75 % of the items on the MISSION-Vet Fidelity measure).*Maintenance*—The degree to which the successful deployment of MISSION-Vet was maintained will come from data collected through the previous components of the RE-AIM model but extended a year beyond the end of the GTO support. Thus, this study will be able to assess whether MISSION-Vet maintains a high Reach, Effectiveness, Adoption, and Implementation between the end of the GTO support and the last data collection wave, which will be a year after the GTO support ends.

*Hypothesis*. We expect better results across all elements of the RE-AIM model in the GTO group than in the IU group.

*Data analysis*. The scores for R, E, A, and I will be calculated among the Veterans in both the GTO and IU groups during the 2-year period of GTO support. For *Reach*, we will perform a *z* test for the comparison of the proportion of Veterans at the end of the GTO period with adequate fidelity between GTO versus IU. The *Effectiveness* analysis will involve *t* tests comparing mean scores at the end of the GTO period for the proportion of time housed and homeless (on the logit scale), components of the ASI, and the GAF. For *Adoption*, we will compare the proportion of case managers through a *z* test who have “adopted” MISSION-Vet according to the specified measure. We will also perform a logistic regression of whether a case manager adopted MISSION-Vet as a function of study arm, one of the moderating variables, and their interaction, testing specifically for the interaction term. The analysis of *Implementation* will compare through a *z* test the proportion of Veterans who participated in MISSION-Vet who had a fidelity score of at least 75 % between the GTO versus IU groups.

*Maintenance*—The analyses described above for R, E, A, and I will be similarly applied to the data collected and summarized a year after the end of the GTO support period.

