#### Recruitment

The subjects in this study are the HUD-VASH case managers although data about the Veterans on their caseload will also be collected. All case managers were invited to participate and consented before randomization by the study staff. The two sub-teams from each site that were assigned to GTO or IU have approximately equal numbers of case managers and vouchers, although the exact numbers shift frequently due to staff turnover and Veteran dropout, graduation, and the issuing of new vouchers. Regardless, consistent with cluster random assignment, each case manager is linked to a certain sub-team (and thus study condition), and each Veteran is in turn linked to a specific case manager. If sites decide to add new staff to a sub-team, that case manager would then automatically be assigned to the condition of that sub-team.

All HUD-VASH case managers in both groups will be invited to the webinar training on MISSION-Vet. After MISSION-Vet begins, case managers will be responsible for engaging their Veterans into MISSION-Vet services. Any Veteran participating in HUD-VASH at each of these three sites is eligible to receive MISSION-Vet services. Through training and TA, case managers and peer specialists will be guided to follow the recommended inclusion and exclusion criteria of MISSION-Vet: (1) has a current substance abuse or dependence disorder and a co-occurring mental illness and (2) is willing to participate in MISSION-Vet services. However, the decision with whom to deliver MISSION-Vet will ultimately be made by the case managers. MISSION-Vet takes about 1 year to fully deliver; therefore, Veterans will be invited to take part in MISSION-Vet in the first year of the 2-year intervention period. The study received a waiver of consent to use client-level data already being collected as part of the homeless data program management system of HUD-VASH.

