#### Aim 1: compare MISSION-Vet fidelity between GTO and IU groups

*Data source*. Veterans served by case managers in the GTO and IU groups.

*Measures and data collection.* The MISSION-Vet Fidelity Measure tracks all the core elements of the MISSION-Vet treatment model, including CTI, DRT, peer support, vocational supports, and trauma-informed care for each individual Veteran. The fidelity index consists of 78 items assessing the presence or absence of certain activities within MISSION-Vet. Taking the responses from all non-missing items, we will compute a fidelity score for each Veteran. The data will be extracted from the VA Computerized Patient Record System (CPRS) on all HUD-VASH Veterans served by case managers in the IU or GTO conditions, at each of the three HUD-VASH sites.

*Hypothesis.* We expect that Veterans served by case managers who were in the GTO group will receive MISSION-Vet with greater fidelity compared to those who are in the IU group.

*Data analysis.* We will fit cross-sectional linear random effects (to account for clustering) models for the fidelity score, measured at 12 months post-baseline.

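### Aim 4 Effectiveness is defined only among Veterans with adequate fidelity, a post-randomisation status that GTO is meant to raise, and the analysis paragraph leaves open whether its t tests use that subset

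*Protocol article*

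**What the plan says.** All references are to the Protocol article.

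- **Definition (Aim 4, measures).** The sentence begins "Obtained from aim 3, effectiveness will be the percentage of all eligible Veterans" and, with its restriction, reads "effectiveness will be the percentage of all eligible Veterans *who receive MISSION*-*Vet with adequate fidelity* who improve on each outcome". The restriction is italicised in the source, so it is deliberate. Adequate fidelity is "defined as the endorsement of at least 75 % of the items on the MISSION-Vet Fidelity measure".
- **Both arms (Aim 4, measures).** Each RE-AIM measure "will be calculated for both the IU and GTO groups".
- **Hypothesis (Aim 4).** "We expect better results across all elements of the RE-AIM model in the GTO group than in the IU group". Effectiveness is one of those elements.
- **What GTO is expected to change (Aim 1).** Veterans of GTO case managers "will receive MISSION-Vet with greater fidelity compared to those who are in the IU group". Reach in Aim 4 uses the same 75 % threshold as an outcome, with all eligible Veterans as denominator.
- **Who gets into the subset (Recruitment).** A recommended criterion is that the Veteran "is willing to participate in MISSION-Vet services", but "the decision with whom to deliver MISSION-Vet will ultimately be made by the case managers".
- **Planned test (Aim 4, data analysis).** Reach, Adoption and Implementation get z tests of proportions. Effectiveness gets t tests of end-of-support means for time housed and homeless, ASI components and the GAF. The paragraph opens by saying the scores are calculated for Veterans of both arms. It neither repeats nor lifts the adequate-fidelity restriction. The same analyses are repeated a year later for Maintenance.

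**The concern.** Adequate fidelity is observed after assignment and is the thing the randomised strategy is meant to move. If GTO succeeds on Reach, the GTO subset contains Veterans whose counterparts under IU did not cross the threshold. The two subsets then differ in who was selected into them, before any effect on outcome. Selection also passes through case managers who know their arm, since the Overview says conventional blinding is not possible. Their choice decides who is offered MISSION-Vet. It does not by itself decide who reaches 75 % of items, so it supports the mechanism only indirectly.

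At stake is the Effectiveness part of the Aim 4 hypothesis, during GTO support and again under Maintenance. A comparison in the restricted set could show a GTO-IU difference where none exists, or hide a real one. It would be reported beside the aim 2 and 3 results and could appear to contradict them.

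**Working it through.** **1. No figure to reproduce.** The article gives no expected value for Effectiveness, and the Power analysis section calls aim 4 exploratory and gives no power for it. Every number below is an assumption chosen to show the mechanism.

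**2. Definition against test.**

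| | Aim 4, measures | Aim 4, data analysis |
|---|---|---|
| Quantity | percentage improved | mean scores |
| Outcomes | those of aim 3 | ASI components and GAF, plus time housed and homeless |
| Population | eligible Veterans with adequate fidelity | not stated beyond Veterans of both arms |
| Test | none given; GTO hypothesised better | t tests |

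The two places agree on neither the quantity nor the outcomes, and the second leaves the population open.

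**3. Hand illustration, no arm effect for any Veteran.** Assume 20 % reach adequate fidelity under IU and 60 % of them improve. Under GTO the same 20 % reach it plus a further 20 %, of whom 40 % improve.

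- IU: 60 %.
- GTO: (0.20 × 0.60 + 0.20 × 0.40) / 0.40 = 0.20 / 0.40 = 50 %.
- Difference: −10 points, all of it from selection.

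In general the spurious difference is (share of the GTO subset that was added) × (improvement in the added group − improvement in the IU group). Here that is 0.5 × (0.40 − 0.60) = −0.10. It is zero if the added Veterans also improve at 60 %, and it favours GTO if they improve more often than that.

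**4. Range.** Let U be a latent tendency to reach fidelity and Y a latent outcome, both standard normal with correlation ρ. Improvement is Y above its 60th percentile, so 40 % improve in each arm and GTO has no effect on outcome. The top share pI of U reaches fidelity under IU, and the top share pG under GTO. Effectiveness as defined is P(improve | U in the top share). With 2,000,000 draws per scenario, GTO minus IU in percentage points is as follows (differences taken before rounding):

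| pI, pG | ρ = 0 | ρ = 0.2 | ρ = 0.4 |
|---|---|---|---|
| 5 %, 15 % | −0.2 | −4.2 (56.5 → 52.3) | −7.7 (73.2 → 65.5) |
| 10 %, 30 % | 0.0 | −4.7 (53.9 → 49.2) | −9.7 (68.4 → 58.8) |
| 20 %, 30 % | 0.1 | −1.9 (51.1 → 49.2) | −4.0 (62.9 → 58.9) |
| 20 %, 50 % | 0.1 | −4.9 (51.2 → 46.3) | −10.1 (62.7 → 52.6) |

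The brackets give IU → GTO in per cent. The values at ρ = 0 are simulation noise around zero. With all eligible Veterans as denominator, both arms show 40 % in every scenario and the difference is 0.

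The mean scores move the same way. At 10 % and 30 % with ρ = 0.4, the mean of Y is 0.237 standard deviations lower under GTO. Testing means in place of a percentage therefore does not remove the problem if the restricted set is used.

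The sign is built into this model: with positive ρ the added Veterans always have the poorer prognosis. A negative ρ would reverse it.

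**The case against.** The strongest reply has three parts.

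**The document never says it will test the restricted percentage.** This stands. The only stated Effectiveness test is of means, in a population that is not restated, so a reader who infers that the 60 % against 50 % quantity will be tested goes beyond the text. But reading the data analysis paragraph as all Veterans does not rescue the plan. It would contradict the italicised definition, and the hypothesis would still claim a GTO advantage on the measure as defined.

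**The unrestricted comparison already exists.** This also stands. Aims 2 and 3 compare housing, mental health, substance use and functioning by arm with repeated-measures random effects models and no fidelity threshold. Their hypotheses mention Veterans who receive MISSION-Vet, but the 75 % rule does not appear there. A reader might infer that the trial's conclusions about Veteran outcomes are compromised. They are not, because those conclusions rest on aims 2 and 3.

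**The restriction is intended and the aim is exploratory.** Aim 4 describes Effectiveness as efficacy when conditions are ideal and treats RE-AIM as a heuristic, while Reach captures non-delivery separately. That justifies describing outcomes among adequately treated Veterans within each arm. It does not justify a GTO-IU inference on a subset formed after randomisation, and the exploratory label lowers the consequence without removing the bias.

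**Conclusion.** The point holds for one exploratory measure. Effectiveness is defined on a post-randomisation subset that GTO is meant to enlarge, a GTO advantage is hypothesised on it, and the analysis paragraph does not settle which Veterans enter the t tests. If the restricted set is used, the arm comparison is open to selection bias.

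The size is not fixed by the document. It is about 0 if reaching fidelity is unrelated to prognosis. It is 1.9 to 4.9 points against GTO at an assumed correlation of 0.2, and 4.0 to 10.1 points at 0.4, for the assumed shares shown. A reader might infer that the bias must run against GTO, on the ground that the added Veterans are harder to engage. No section says who they would be, so the direction is as uncertain as the size.

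**What to change.** Reconcile the Aim 4 measures and data analysis paragraphs.

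1. State that the between-arm Effectiveness comparison, and its repeat under Maintenance, uses all eligible Veterans by sub-team as randomised and regardless of fidelity, in line with aims 2 and 3.
2. Say which Veterans count as eligible, using facts that the arm cannot influence. Willingness to take part is expressed after assignment and should not define the set.
3. Align the quantity and the outcomes, so that definition and test both use either means or the percentage improved, and say whether housing is included.
4. Keep the percentage improved among adequate-fidelity Veterans as a within-arm description with no GTO-IU inference, and word the Aim 4 hypothesis so that its Effectiveness part refers to the comparison in item 1.

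This changes analysis wording only. Fidelity data are already extracted for all HUD-VASH Veterans served in both arms, and the outcomes come from HOMES. The downside is that Veterans who did not receive the programme dilute the effect, and Effectiveness then overlaps in part with aims 2 and 3.

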
### Measures, procedures, and analyses by study aim

All of the below measures will be collected for 3 years: during the 2-year GTO period of support and 1 year after that support ends to assess sustainability (see aim 4 below).

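### Invitations in year 1 and about a year of delivery leave few or no Veterans in MISSION-Vet late in year 3, so maintained Reach, Adoption and Implementation would not show sustained staff practice

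*Protocol article*

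**What the plan says.** The Recruitment section of the protocol article states that "MISSION-Vet takes about 1 year to fully deliver" and draws the consequence that "Veterans will be invited to take part in MISSION-Vet in the first year of the 2-year intervention period". The section on measures, procedures and analyses says that all measures are collected "during the 2-year GTO period of support and 1 year after that support ends to assess sustainability".

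Under Aim 4, Maintenance "will come from data collected through the previous components of the RE-AIM model but extended a year beyond the end of the GTO support". The article says the study can judge whether Reach, Effectiveness, Adoption and Implementation stay high "between the end of the GTO support and the last data collection wave, which will be a year after the GTO support ends". The analysis paragraph adds that the analyses of those four components "will be similarly applied to the data collected and summarized a year after the end of the GTO support period".

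Three of the four components depend on MISSION-Vet being delivered:

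- Reach and Implementation need adequate fidelity, "defined as the endorsement of at least 75 % of the items on the MISSION-Vet Fidelity measure". Implementation is taken among Veterans who took part.
- Adoption is "The proportion of case managers who have more than 50 % of their eligible Veterans engaged in MISSION-Vet".
- The fidelity data come from a note template that staff complete when they deliver MISSION-Vet (section on the GTO implementation strategy).

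**The concern.** The invitation year and the length of a course were chosen together so that a full course fits inside the two years of support. Nothing comparable is planned for the year after. The same measures are carried into that year without saying who could be receiving MISSION-Vet then, or which notes count.

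Sustainability after support ends is the stated reason for the third year of data. If the year-3 values of Reach, Adoption and Implementation are set mainly by the invitation calendar, by notes carried over from earlier, and by Veterans joining and leaving caseloads, they could be reported as practice maintained or lost when they say little about what case managers did once GTO support was withdrawn.

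**Working it through.** **Inputs from the article.** Support lasts 24 months. Follow-up after support lasts 12 months. Invitations fall in months 0–12 of the intervention period. Delivery takes about 12 months. The fidelity measure has 78 items with a 75% threshold. The rate of caseload turnover is not given.

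**The plan's own timeline.** 24 + 12 = 36 months, which reproduces the stated 3 years. Maintenance therefore occupies months 24–36, with the last wave at month 36.

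**Planned end of delivery.** Latest invitation + length of course = 12 + 12 = month 24. On the plan's own schedule, 0% of invited Veterans are in MISSION-Vet after month 24.

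**If delivery overruns.** Assume invitations spread evenly over months 0–12 and a course of D months (12 to 24). The share still active just after month 24 is (D − 12)/12. The share of all delivery time that falls in year 3 is (D − 12)² / (24 × D).

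- D = 13: 1/12 = 8% active; 1/(24 × 13) = 0.3% of delivery time.
- D = 15: 3/12 = 25% active; 9/(24 × 15) = 2.5%.
- D = 18: 6/12 = 50% active; 36/(24 × 18) = 8%.

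The last course ends at month 12 + D, which is month 30 when D = 18. So none of these cases leaves anyone active at month 30 or later.

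**If support starts before the invitation year.** Trial status dates the first planning meetings January to November 2013 and the start of fidelity data April 2013 to January 2014. If the ends of those ranges refer to the same sites, the lag is 3 months (January to April) and 2 months (November to January). With a lag of k months and 12-month courses, the share active just after support ends is k/12: 17% for k = 2, 25% for k = 3 and 50% for an assumed k = 6. The last course ends at month 24 + k, so at most month 30, and nobody is active at month 36.

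**What the measures then show.** The article does not say whether year-3 scores accumulate over all of a Veteran's notes or use year-3 notes only.

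- *Cumulative.* For an unchanged group with no new delivery, Reach at month 36 equals Reach at month 24. If a fraction f of the eligible caseload has been replaced by Veterans who were never invited, and leaving is unrelated to fidelity, Reach at month 36 = (1 − f) × Reach at month 24. On the year-1 schedule the change is driven by f. Adoption behaves in the same way if engaged means ever engaged.
- *Year-3 notes only.* The threshold is 0.75 × 78 = 58.5, so at least 59 items if none is missing. With no course under way, Reach and Adoption are near zero in both arms, and Implementation has almost no participants in its denominator.

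**Effectiveness.** Housing, Addiction Severity Index components and the GAF are recorded in HOMES whether or not MISSION-Vet is under way. They can still be compared a year after support ends.

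**The case against.** The strongest reply is that the article never closes enrolment. The year-1 statement can be read as making sure that a full course fits within the support period. It is silent on the year after. Any HUD-VASH Veteran at the sites is eligible, case managers decide whom to treat, and GTO aims to make the practice routine. On that reading, low use in year 3 would be a genuine finding about sustainment. This stands as a possible reading. But the discretion given to case managers concerns whom they treat, and nothing in the article says that invitations continue or resume after year 1. The two sections still need to be reconciled.

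A reader might infer that Maintenance cannot be assessed at all, or that the result must be either 100% or 0% maintained. The documents support neither. The Effectiveness part remains computable from HOMES. Caseloads change often, so even cumulative values move, and an overrun or an early start of support leaves a tail of Veterans early in year 3. If staff do start new Veterans, the values also respond to practice.

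A reader might also fault the between-arm test at month 36 for not testing whether a level was held. The stated hypothesis is itself that GTO does better than implementation as usual on every component, and a between-arm comparison addresses that. Reporting the change as well is an improvement, not a correction.

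Finally, Aim 4 is described as exploratory, and a condensed article may leave scoring windows to a fuller document. The first lowers the weight. The second does not remove the point, because the tension lies between two statements that the article itself makes.

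**Conclusion.** The point holds for Reach, Adoption and Implementation. On the schedule as written, delivery ends at about month 24. Under the overruns examined (up to 18 months) and the early starts examined (up to 6 months), between 8% and 50% of invited Veterans are active just after support ends, and none at the last wave. The year-3 values would then reflect the calendar, carry-over and turnover more than sustained staff practice, so the claim that the study can assess maintenance of these three components is not supported as the article stands.

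This rests on three assumptions: invitations stay within year 1, they are spread evenly over it, and courses last about as long as stated. If new starts continue in year 3, the measures become informative, but their window and denominator still have to be fixed.

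The severity is moderate. Aim 4 is exploratory, its Effectiveness component is unaffected, and Aims 1–3 do not depend on it.

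**What to change.** Reconcile the Recruitment section with the Maintenance text under Aim 4 by stating whether the year-1 limit only defines the cohort for Aims 1–3 or also ends new starts.

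- *If staff may keep starting Veterans:* compute Maintenance Reach, Adoption and Implementation from fidelity notes dated in the 12 months after support ends, among Veterans eligible in that year, including new voucher holders. Compare them with a 12-month window during support that is named in advance and scored in the same way. Report the change by arm next to the planned between-arm comparison.
- *If invitations stop after year 1:* limit Maintenance to the durability of Veteran outcomes and withdraw the claim for the other three components.

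The cost is wording and analysis programming, since the measures are already to be collected for 3 years. The drawback is that a 12-month window holds few completed courses: with a course of about a year, only Veterans who start near month 24 can finish by month 36. Fewer Veterans will therefore reach the 75% threshold, which is why the comparison window must have the same length.

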### Participation sites and recruitment

#### Site composition

This study includes three large HUD-VASH sites: site A (450 HUD-VASH vouchers and 18 case managers), site B (850 HUD-VASH vouchers and 27 case managers), and site C (810 HUD-VASH vouchers and 24 case managers), for a total of 2110 HUD-VASH vouchers and 69 case managers. Case manager and voucher numbers were based on a point in time and are expected to change as new vouchers are issued over time. Each site has naturally occurring sub-teams of case managers (sites A, B, and C each has two clusters), which will be randomized with equal probability to IU or GTO by the team statistician using a random number generator. We chose to randomize case managers within each of these sites because it holds constant the variation due to site-level characteristics, funding streams, regulations, data collection activities, and political climates.

During the planning of the study, the three HUD-VASH programs were selected because they were similar across many key factors. For example, the number of vouchers allocated to each site is close to 500 with 85–95 % of these vouchers in use at each site. HUD-VASH case managers at each site are typically expected to have contact with each Veteran at least once per month—with a goal of contacting the Veteran at the Veteran’s residence once he/she has been housed. While some Veterans need more frequent contact, no Veteran gets less than this amount at any site. Among the Veterans in HUD-VASH at these sites, the VA Homeless Network Coordinators report approximately 90 % having substance use and/or mental health diagnoses. Additionally, each of these sites reports that approximately 75 % of Veterans in HUD-VASH receive other services at the VA or in the community beyond standard HUD-VASH case management services.

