#### Aim 2: compare the effect on the proportion of time the Veteran is housed between GTO and IU groups

*Data sources*. Veterans served by case managers in the GTO and IU groups.

*Measures and data collection*. For each Veteran entering HUD-VASH, a case manager must complete a HUD-VASH Referral Worksheet that contains the program’s first assessment of days of homelessness and housing. Then, case managers provide data every 3 months on the number of days housed in the last 90 days using the Housing Progress Report form. Case managers are also required to report when a Veteran loses their housing voucher each month. These reports are stored in national database called HOMES (Homeless Operations, Management and Evaluation System).

*Hypothesis*. We expect that Veterans assigned to case managers in the GTO group, who receive MISSION-Vet, will have more days housed in the prior 3 months compared to Veterans who receive MISSION-Vet from case managers in the receiving IU group.

*Data analysis*. Again, we will fit repeated measures linear random effects models in this analysis. As a secondary analysis, we will perform a *z* test for the comparison of the proportion of Veterans at the end the study who have retained their housing (versus lost their voucher) between GTO versus IU.

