#### Aim 3: compare mental health, substance use, and functional outcomes among Veterans served by HUD-VASH case managers in GTO and IU groups

*Data sources*. Veterans served by case managers in the GTO and IU groups.

*Measures and data collection*. In addition to housing, the HUD-VASH staff complete data collection forms for HOMES on four outcomes each month. HOMES requires case managers to make separate ratings on mental health, substance abuse, and associated problems for each Veteran using components of the Addiction Severity Index [46] as well as the Global Assessment of Functioning (GAF) [47].

*Hypothesis*. We expect that Veterans served by HUD-VASH case managers supported by GTO, who received MISSION-Vet, will have improved mental health, substance use, and functional outcomes compared to Veterans served by HUD-VASH case managers in the IU group.

*Data analysis*. We will again fit our repeated measures linear random effects models to the response variables mentioned above.

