For aims 2 and 3, we will focus on the subsample of Veterans in the study for whom we have 12 months of data collected over consecutive 3-month intervals. Because these Veterans serve as their own controls relative to time, they provide the greatest power in detecting the effect of MISSION-Vet + GTO. With the same design effect as in aim 1, the effective sample size available for aims 2 and 3 controlling for clustering is 356 Veterans. For a linear repeated measures model with two treatment groups and five measurements per unit (that is, one every 3 months for a year, including baseline), and assuming a sample of 356 units to randomly divide approximately equally between the two groups, the time-by-intervention effect size that can be measured with 80 % power is 0.082. By convention, this is considered a very small effect size, and it is also small compared to the ones found above in the drug abuse prevention study. We therefore anticipate detecting effects with sufficient power for aims 2 and 3.

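### The exploratory Aim 4 Effectiveness and Maintenance comparisons are t tests of end scores that use neither the earlier HOMES values nor a clustering term, unlike the Aim 2 and 3 models of the same outcomes

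*Protocol article*

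**What the plan says.** Under Aim 4, Data analysis, the Effectiveness comparison consists of t "tests comparing mean scores at the end of the GTO period for the proportion of time housed and homeless" (on the logit scale), and of the ASI components and the GAF. The Maintenance paragraph applies the same analyses to data summarised a year after GTO support ends. Neither names a baseline value, a change score, a covariate or a random effect.

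Other parts of the article bear on this choice:

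- Aim 4, Measures, defines Effectiveness as the percentage of eligible Veterans with adequate fidelity "who improve on each outcome in an amount consistent with a statistically significant effect".
- Aim 2 says that the referral worksheet "contains the program’s first assessment of days of homelessness and housing", with housing reports every 3 months after that.
- Aim 3 says that "the HUD-VASH staff complete data collection forms for HOMES on four outcomes each month".
- Aims 2 and 3 analyse these outcomes with repeated measures random effects models. The Power analysis describes "five measurements per unit (that is, one every 3 months for a year, including baseline" and gives the reason: "Because these Veterans serve as their own controls relative to time, they provide the greatest power".
- Site composition states that "sites A, B, and C each has two clusters", which makes six randomised sub-teams, three per arm.
- The Power analysis calls Aim 4 exploratory and gives it no power calculation.

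**The concern.** The same outcomes are handled in two ways. Aims 2 and 3 use each Veteran's own earlier values and random effects. Aim 4 drops both without giving a reason, and its test of end scores does not measure the improvement by which Effectiveness is defined.

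This has three consequences. Precision is lost whenever baseline and end scores are correlated. With only six sub-teams, the arms may start some way apart by chance, and a comparison of end scores passes on part of that gap. And a Veteran-level t test treats Veterans who share a case manager and sub-team as independent, so its standard error is too small.

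What is at stake is the RE-AIM Effectiveness result and its one-year repeat. The article sets a directional hypothesis for these, expecting better results under GTO on every RE-AIM element.

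**Working it through.** **1. The plan's own figure.** Aim 4 has none. The nearest is the Aim 1 figure for an unadjusted two-sample t test. Inputs from the Power analysis: 1604 Veterans, 66 case managers, m = 24.3, ICC = 0.15, alpha 0.05 (taken as two-sided), 80 % power.

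- Deff = 1 + (24.3 − 1)(0.15) = 4.495.
- Effective N = 1604 / 4.495 = 356.8, the plan's 356, or 178 per arm.
- Detectable effect = (1.960 + 0.842) × √(2/178) = 0.297. The noncentral t gives 0.298, as stated.

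**2. Precision lost by omitting baseline.** Adjustment leaves a fraction 1 − r² of the variance, where r is the correlation between baseline and end score. The article gives no r, so a range is assumed. The last column applies √(1 − r²) to the Aim 1 figure of 0.297 as an illustration only.

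| r (assumed) | Cut in residual variance (r²) | SE multiplier √(1 − r²) | Illustrative detectable effect |
|---|---|---|---|
| 0.3 | 9 % | 0.954 | 0.283 |
| 0.5 | 25 % | 0.866 | 0.257 |
| 0.7 | 49 % | 0.714 | 0.212 |

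**3. Chance baseline difference between arms, in SD units.**

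- Case-manager clustering only, 33 v 33 case managers: √(2 × (0.15 + 0.85/24.3) / 33) = 0.106. Had Veterans been randomised individually, 802 v 802, it would be √(2/802) = 0.050.
- Sub-team clustering only, 3 v 3 sub-teams of 1604/6 ≈ 267 Veterans: √(2[ICC + (1 − ICC)/267] / 3). The sub-team ICC is not given. Assumed values of 0.01, 0.02 and 0.05 give SDs of 0.10, 0.13 and 0.19. The chance of a difference above 0.2 SD is then about 4 %, 11 % and 29 %. These figures ignore the pairing of sub-teams within site, which helps only if the analysis uses site. The t test does not.
- An end-score contrast carries r × the baseline difference. A 0.2 SD difference puts 0.06, 0.10 or 0.14 SD into the result at r = 0.3, 0.5 or 0.7.

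**4. Standard error without a clustering term.** A Veteran-level t test understates the standard error by √Deff. The true type I error at nominal 0.05 is 2 × [1 − Φ(1.96/√Deff)].

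| Case | Deff | √Deff | Type I error |
|---|---|---|---|
| Plan's values: m = 24.3, ICC 0.15 | 4.495 | 2.12 | 36 % |
| Smaller ICC, assumed 0.05 | 2.165 | 1.47 | 18 % |
| Fewer Veterans per case manager, assumed m = 10, ICC 0.15 | 2.35 | 1.53 | 20 % |

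The last two rows matter because the plan calls 0.15 conservative, and because m falls if only Veterans with adequate fidelity are analysed. Clustering by sub-team, the unit randomised, would add to all three.

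**The case against.** Much can be said for the plan. Aim 4 is exploratory, RE-AIM serves there as a heuristic, and the main tests of housing, ASI and GAF already use baseline. An unadjusted comparison of end scores in a randomised trial is not wrong in itself. These points stand and limit the finding to a secondary summary.

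A reader might infer that Aim 4 has 80 % power, rising to 90 % with adjustment at r = 0.5. The documents do not support that. The effective N of 356 and the effect of 0.298 belong to Aim 1. They already include a design effect that the Aim 4 t test lacks, and the number of Veterans with adequate fidelity is unknown. A low r is also plausible: the gap is up to two years, or three for Maintenance, and the first housing value is a referral assessment.

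A reader might also infer that the Aim 4 result is confounded. Chance imbalance under randomisation is sampling error, which a correct cluster-level standard error covers. The t test as named does not supply one. If only Veterans with adequate fidelity are compared, selection after randomisation may add differences that baseline adjustment does not reliably remove.

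Two general statements could be read as covering Aim 4. Design challenges says that case-manager clustering is accounted for in the analyses. If that reaches Aim 4, the standard-error point falls away for case managers, but the method is then no longer the t test named, and the two places need reconciling. The Power analysis promises control for confounders, but in the Aim 1 paragraph, about fidelity, and without naming the baseline outcome.

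**Conclusion.** The point holds for Effectiveness and Maintenance in the exploratory Aim 4 and no further. As named, the t tests discard information that the article uses for the same outcomes in Aims 2 and 3, and they do not match the definition of Effectiveness as improvement.

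The cut in residual variance forgone is 9 % to 49 % for an assumed r of 0.3 to 0.7. Chance baseline differences enter the estimate in proportion to r. The neglected clustering weighs more: at the plan's own design effect the standard error is too small by a factor of about 2.1. That assumes the test is run on individual Veterans without correction, and the factor is smaller at a lower ICC or with fewer Veterans per case manager.

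It would go too far to conclude that the trial's findings on housing, mental health, substance use or function are undermined. The main conclusions of Aims 2 and 3 are unaffected.

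**What to change.** Replace the Effectiveness and Maintenance t tests with the random-effects model of Aims 2 and 3, including site and the baseline value of the same outcome. Take the arm contrast at the end of the GTO period and again one year later, each with a 95 % confidence interval. The power calculation for Aims 2 and 3 covers 12 months, so the model has to run over the later reports, which the article says are collected for 3 years.

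Define baseline as the last HOMES value before MISSION-Vet starts at the site. For the ASI components and the GAF, that such values exist is inferred from the monthly forms, so availability should be confirmed. Veterans who enter later have only an entry value. Analyse them in a stated sensitivity analysis and not with a missing indicator, which is not clearly safe when entry follows randomisation. State also whether the comparison covers all eligible Veterans or only those with adequate fidelity.

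The cost is a little more analysis work and a rule for late entrants. No new data collection is planned for this.
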